### Dissemination

At the end of the IMP^2^ART programme, we will write summaries providing feedback to the practices, including a lay summary suitable for sharing on the practice website.

At the end of the trial, we will hold workshops in each of the three research sites (London/Sheffield/Edinburgh) to which we will invite key stakeholders and participating practices. The aim will be to share preliminary findings and invite discussion on the interpretation and implications, to gauge applicability of our findings to a broader range of practices and contexts [77], and to maximise the study’s reach by inviting a broad range of stakeholders (patient groups, healthcare professionals, managers and commissioners, academics) not involved in IMP^2^ART. In addition, we will disseminate findings to healthcare practitioners, healthcare planners and policy makers, and also professional audiences, grant holders. Collaborators will use their professional networks to raise awareness of the programme of work.

Conference abstracts and peer-reviewed publications will report findings throughout the programme grant, with key publications in high-impact journals. We have adopted the terminology and will follow the StaRI reporting standards for implementation studies [43].

The authorship policy follows the ICMJE criteria for academic publications (http://www.icmje.org). If the journal allows, all publications resulting from IMP^2^ART programme will include in the authorship list ‘the IMP^2^ART Group’. Links to publications will be sent to practices that participated in the trial. Finally, we will use the innovative dissemination channels of the Asthma UK Centre for Applied Research (AUKCAR) [https://www.ed.ac.uk/usher/Aukcar] (websites/blogs/twitter/public lectures) to raise awareness of our publications. Asthma + Lung UK will support dissemination and promotion of our findings to their patient and scientific audiences using their digital and social media platforms.

## Discussion

This trial will test whether a whole system implementation programme (IMP^2^ART) can improve supported self-management for asthma in routine primary care practice in England and Scotland, as measured by a reduction in unscheduled care and an increase the provision of asthma action plans provided.

### Strengths and limitations

A major strength of the study is the robust randomised controlled design. Additionally, the trial and the implementation components have been designed by a multidisciplinary team, including engagement with PPI colleagues and professional stakeholders currently working in primary care, strengthening the applicability to real-world practice. The extensive developmental phases have ensured that the components of the implementation strategy are theoretically based and revised after feasibility testing [28, 49–58]. However, the trial has a number of limitations; for example, late-2020 changes to the QOF to include a written personalised action plan [78] may influence English practices interest in supported self-management, though this will affect practices in both groups equally. Use of routine data allows assessment of the impact of implementing supported self-management in the population of all clinically eligible people with asthma, and our procedures for blinding of routine data extraction, handling and analysis reduce bias. Although we cannot eliminate coding discrepancies, our preliminary work has enabled us to describe the likely impact on our outcomes. Finally, although the implementation strategy was adapted for a COVID-19 context, it is uncertain what implications the pandemic may have had on the trial, although again, this will affect practices in both groups equally.

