## Methods

### Study design and settings

The trial uses a parallel group, hybrid II (addressing both implementation and clinical outcomes) [42] cluster randomised controlled implementation trial design (randomisation at the general practice level), testing the implementation of an evidence-based and guideline-recommended intervention. The trial will be conducted in general practices across England and Scotland. The protocol adopts the principles and terminology of the Standards for Reporting Implementation studies (StaRI) [43], uses the Template for Intervention Description and Replication (TIDieR) guide [44] to describe the implementation strategy and follows the SPIRIT checklist [45] (Additional file 1) to report the trial methodology. In addition, the CONSERVE-SPIRIT checklist [46] guides reporting of modifications due to the COVID-19 pandemic.

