**Fig. 1 Fig1:**
[figure not shown]
SPIRIT figure of enrollment, interventions and assessments

To be eligible, practices must use one of the four common electronic health record (EHR) systems (EMIS, SystmOne, Vision or Microtest) for which components of our implementation strategy have been designed, and agree to Optimum Patient Care (OPC: a social enterprise that leads quality improvement initiatives involving routine data extraction from practices https://optimumpatientcare.org) extracting anonymised routine coded data to measure the primary and other outcomes of the study. A successful extraction of data is a requirement to (a) demonstrate that there are no insurmountable governance or technical problems, (b) establish that the practice data would allow assessment of the primary health outcome, and (c) for use in the baseline audit and feedback reports.

Practices will be of varying sizes (to reflect the range of UK primary care) and thus have different numbers of ‘active asthma’ patients. Active asthma is defined by the UK Quality and Outcome Framework (an annual reward and incentive programme for all general practices in England) as having a coded diagnosis of asthma and having been prescribed an asthma medication within the previous year [47]. Our sample size calculation takes variable cluster size into consideration, but we will exclude very small practices likely to have substantially fewer than 200 patients with ‘active asthma’ registered throughout the trial. (Note: this will be an estimate at the time of recruitment as we will not know the exact cluster sizes until the final routine data are available at the end of the trial). Finally, we will exclude practices undertaking research or initiatives that might affect our outcomes, and practices that work closely with another participating practice (e.g. as part of a network or federation). Decisions about potential contamination will be overseen by a sub-committee (chaired by [name]).

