### Randomisation

The unit of randomisation will be the general practice. Remote online randomisation (1:1 implementation:control) will be provided by the Pragmatic Clinical Trials Unit (PCTU), Queen Mary University of London. Stratifiers, determined according to contextual influences identified during developmental work [50, 51], will be deprivation status (less deprived, ≤ median deprivation score/more deprived, > median deprivation score), practice list size (small, ≤ 8035 patients; large, > 8035 patients) and GP training status of the practice (yes/no). In a second step, 32 practices will be randomly selected for quality improvement questionnaire data collection, ensuring that these practices are distributed evenly between the implementation and control groups. Randomisation is implemented in REDCap (Research Electronic Data Capture) software [69] and allocations will be requested by the programme manager (VH).

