### Statistical analysis

Analysis will be on data at 12 months (implementation/process outcomes) and 24 months (health outcomes) follow-up. Individuals will be included in the analysis only if they were registered in a practice at baseline, 12 months and 24 months follow-up. Practices will be analysed in the group to which they were allocated regardless of compliance (intention-to-treat). The target of estimation is the average treatment effect across participants in terms of the primary clinical as well as primary implementation outcome. An unweighted independence estimating equation analysis on participant-level data will be used to estimate the participant-average difference in proportions between groups. This model employs an independence working correlation structure in conjunction with robust standard errors to account for clustering. Secondary outcomes will be analysed using the same or a similar model appropriate for the respective variable type. The models will include fixed effects for stratification variables and may incorporate additional individual-level covariates as fixed effects (covariates are limited as we are taking them from routine data). A fully pre-specified model will be provided in the statistical analysis plan (SAP). Treatment effect estimates, with associated confidence intervals and *p*-values, and ICCs will be reported for each outcome.

The primary clinical outcome as well as the secondary outcomes of unscheduled care (12 months), asthma attacks and prescribing outcomes will, by definition, not have any missing data as the absence of a code describing an event or prescription is defined as the binary variable value ‘no’. Patterns and amount of missing data for questionnaire outcomes and other routine data variables will be explored, and a suitable multiple imputation method used. The strategy for dealing with missing values will be articulated in detail in the SAP which will be prepared by the Pragmatic Clinical Trials Unit (PCTU) statisticians in consultation with other blinded research team members. Allocation codes will not be released to the statisticians before the SAP is signed off and made publicly available.

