### Trial status

*Protocol version:* 4.0, 19/04/22.

*Recruitment:* General practice recruitment began in January 2021, and we anticipate finalised randomisation at end of March 2023.

*Trial status:* Ongoing.

*Sponsor*: ACCORD, Royal Infirmary of Edinburgh, [name].

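### The England-only QOF action-plan change is balanced between arms only in expectation; country should be a model term for the action-plan and review outcomes, with one arm-by-country estimate

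*Protocol article*

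**What the plan says.** Under Strengths and limitations, the protocol article names "late-2020 changes to the QOF to include a written personalised action plan" as a limitation and then says it "may influence English practices interest in supported self-management, though this will affect practices in both groups equally". Under Practice eligibility criteria and recruitment, it describes the QOF as "an annual reward and incentive programme for all general practices in England". Under Study design and settings, it says "The trial will be conducted in general practices across England and Scotland". Under Trial status, "General practice recruitment began in January 2021", so the change was in place before any practice was randomised.

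Action-plan ownership by questionnaire at 12 months is the primary implementation outcome. Recorded provision of action plans and the proportion of patients reviewed are secondary outcomes from routine data (Table 2).

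Under Randomisation, "Stratifiers, determined according to contextual influences identified during developmental work" are three: deprivation status, list size and GP training status. The 32 questionnaire practices are then drawn so that the arms have equal numbers; no other balancing factor is given. Under Statistical analysis, "The models will include fixed effects for stratification variables and may incorporate additional individual-level covariates as fixed effects", and the complete model is deferred to the SAP.

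**The concern.** The QOF change rewards the same behaviour that the implementation strategy promotes, and by the article's description it applies in one of the trial's two countries. Usual care for the action-plan outcomes may therefore differ between English and Scottish practices.

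The reassurance that both groups are affected equally covers less than it seems to.

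- **Balance.** Equal exposure is what randomisation delivers on average. In one realised allocation, and above all in a comparison of 16 practices with 16, the country mix can differ between arms, and nothing in the stated design limits that.
- **Effect.** Even with identical exposure in both arms, the difference between strategy and usual care need not be the same with the incentive as without it.

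At stake are some precision for the primary implementation outcome and the interpretation of a pooled effect that spans two payment settings.

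**Working it through.** **Inputs from the protocol article.** h = 0.322; 203 per arm before clustering; 20 questionnaires from each of 16 practices per arm; ICC 0.03 for ownership; ICC 0.07 for unscheduled care; 140 practices after withdrawal; mean cluster size 200 with coefficient of variation 0.8. Ownership is about a third in controls plus 15 points, so it averages about 0.4.

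**Assumed, because the article does not give them.** A quarter of practices are Scottish (8 of 32; range 6 to 10). The England-Scotland gap in ownership is 10 to 15 points.

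**1. The plan's own figure.** n = 2 × ((1.960 + 1.282)/0.322)² = 202.7, so 203 per arm. Design effect = 1 + 19 × 0.03 = 1.57. Practices per arm = 203 × 1.57/20 = 15.9, so 16. The stated size reproduces.

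**2. Standard error of the ownership difference.** With p(1 − p) = 0.4 × 0.6 = 0.24:
- between-practice variance = 0.03 × 0.24 = 0.0072
- sampling variance of a practice proportion = 0.97 × 0.24/20 = 0.01164
- total per practice = 0.01884
- SE = √(2 × 0.01884/16) = 0.0485, about 4.9 points.

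**3. Chance of country imbalance.** Allocation ignores country, so the number of Scottish practices in one arm is hypergeometric (32 practices, K Scottish, 16 drawn). The probability that the arms differ by 4 or more Scottish practices is 17% for K = 6, 22% for K = 8 and 25% for K = 10. For K = 8, the standard deviation of the arm difference in Scottish share is 15.6 percentage points. It moves the unadjusted ownership difference with standard deviation 0.156 × 10 = 1.6 points to 0.156 × 15 = 2.3 points. A 6:2 split moves it by 4/16 × 10 = 2.5 to 4/16 × 15 = 3.75 points. All are below one SE.

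**4. What a country term would gain.** Variance between practices due to country = gap² × 0.25 × 0.75.

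| Assumed gap | Country variance | Share of 0.0072 | SE after removing it | Reduction in SE |
|---|---|---|---|---|
| 10 points | 0.00188 | 26% | √(2 × 0.01697/16) = 4.6 points | 5% |
| 15 points | 0.00422 | 59% | √(2 × 0.01462/16) = 4.3 points | 12% |

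Estimating one extra coefficient from about 30 practices inflates the variance by roughly 1/30, or the SE by a factor of about 1.017. The net reduction is then about 3% to 10%. A 20-point gap would give 0.0075, more than the whole between-practice variance, so it does not fit the plan's ICC and is not used.

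**5. Precision of an arm-by-country estimate.**
- Questionnaire ownership, Scottish practices 4 v 4 and English 12 v 12: SE = √(0.01884 × (2/4 + 2/12)) = 11.2 points, 95% CI about ±22 points.
- Recorded provision over 140 practices, a quarter Scottish (17.5 v 17.5 and 52.5 v 52.5), keeping p(1 − p) = 0.24 for illustration. Design effect = 1 + (1.64 × 200 − 1) × ICC, which is 10.81 at ICC 0.03 and 23.89 at ICC 0.07. Variance per practice = 0.24 × design effect/200 = 0.0130 or 0.0287. SE = √(variance × (2/17.5 + 2/52.5)) = 4.4 or 6.6 points, 95% CI about ±9 or ±13 points.

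The country comparison is therefore much more informative on recorded provision than on the questionnaire.

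**The case against.** The strongest reply is that the sentence is fair as written. The QOF reaches English practices whatever their allocation, the article discloses the change, and allocation is random. Chance imbalance is not bias, and robust standard errors cover it. That stands, and it limits the point to precision and interpretation.

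Four stronger readings are tempting, and the documents do not support them.

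- **That the final model omits country.** The article names some terms and defers the full model to the SAP. Only absence from the named terms can be stated.
- **That a weak or null result could not be interpreted.** Control ownership is measured by questionnaire, recorded provision is measured in both arms at 12 and 24 months, and the process evaluation examines how national and local context influenced the outcomes. High provision among controls would be visible. These sources do not supply a formal comparison by country.
- **That the contrast must shrink in England.** An incentive could raise control provision and narrow the difference. It could also make practices readier to adopt a review template built to comply with the QOF, and so widen it. The article gives no ownership figure from after the change; its one-third figure comes from a 2014 survey.
- **That the unscheduled-care model needs the same term.** The incentive bears directly on action plans, and there is no argument specific to unscheduled care.

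Two further cautions stand. The Scottish share and the ownership gap are assumptions. List size, already a stratifier and model term, is related to country, since the article mentions many small rural practices in Scotland; it may already absorb part of the gain.

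**Conclusion.** The point holds in a limited form. Describing the effect on the two groups as equal is right for exposure in expectation, but it guarantees neither a balanced country mix in 16 v 16 practices nor a common effect in the two countries. The comparison remains unbiased and its standard errors valid.

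The avoidable loss is modest: about 5% to 12% of the ownership SE, or 3% to 10% after the cost of estimating the term. This rests on a quarter of practices being Scottish, a 10 to 15 point gap, the plan's ICC of 0.03, and no overlap with list size. The possible difference in effect between countries cannot be sized or signed from the article. This is an inexpensive improvement and does not threaten the trial's validity.

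**What to change.** 1. In the SAP, add country (England/Scotland) as a practice-level fixed effect in the models for action-plan ownership, recorded action-plan provision and asthma reviews, if it is not already there. The article says allocation codes are held back until the SAP is signed off, so this can be settled blind.
2. Pre-specify one arm-by-country estimate with a confidence interval, mainly for recorded provision across all practices. Report the same estimate for questionnaire ownership as exploratory, with its imprecision stated.
3. Reword the limitation to say that exposure to the QOF change is balanced between arms in expectation, while the difference between strategy and usual care in England may not match that in Scotland. Do not commit to a direction.

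Cost: one known covariate, one degree of freedom, one additional reported estimate and a changed sentence. No new data collection is needed. The Scottish estimate will be imprecise.

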### Desired impact

Supported self-management has been recommend by asthma guidelines for three decades, but the challenge of implementation means that only a minority of people with asthma benefit from the improved outcomes that it offers. IMP^2^ART explicitly addresses this challenge in the context of routine UK primary care and will inform future implementation and potentially improve the lives of people living with asthma.

### Trial status

*Protocol version:* 4.0, 19/04/22.

*Recruitment:* General practice recruitment began in January 2021, and we anticipate finalised randomisation at end of March 2023.

*Trial status:* Ongoing.

*Sponsor*: ACCORD, Royal Infirmary of Edinburgh, [name].

## Data Availability

Due to the confidentiality of NHS routine data required for this trial, data will not be made available.

## Abbreviations

A&E: Accident and emergency
COVID-19: Coronavirus disease 2019
EHR: Electronic health record
GP: General Practitioner
HS&DR: Health Service and Delivery Research
ICC: Intraclass correlation
IMP^2^ART: IMPlementing IMProved Asthma self-management as RouTine
NIHR: National Institute for Health Research
OID: Organisational Information Document
OPC: Optimum Patient Care
PCTU: Pragmatic Clinical Trials Unit
PPI: Patient and Public Involvement
QALYs: Quality-adjusted life years
QOF: Quality and Outcomes Framework
RCP3Qs: Royal College of Physicians 3 Questions
RCT: Randomised controlled trial
REC: Research Ethics Committee
UK: United Kingdom
